#### Objective IIIb

The second exploratory objective is to evaluate the influence of ALLWheel on objective LTPA (actigraphy).

#### Objective IIIc

The third exploratory objective is to evaluate the influence of ALLWheel on subjective LTPA, barriers to LTPA, motivation, psychological needs satisfaction, and satisfaction with participation.

#### Objective IIId

The fourth exploratory objective is to explore potential mediating and moderating relationships between LTPA and sociodemographic factors, epidemiological variables, and all secondary outcomes.

##### Design

A three-site, pre-post feasibility study will be done.

##### Participant Recruitment

A convenience sample of 12 community-dwelling individuals living with SCI will be recruited through community partners (eg, Adaptavie, Viomax, and Spinal Cord Injury British Columbia) and clinical partners (eg, outpatient rehabilitation programs at each site) that are the knowledge users of the ALLWheel program and who will be involved in the development and refinement of the program. According to Hertzog [61], 10 to 15 participants may be adequate to detect feasibility in a pilot study. Since the primary purpose of this study is to assess feasibility of the ALLWheel protocol for a future clinical trial, from a pragmatic perspective of future recruitment in a relatively small population, a smaller sample size is justifiable. Participants will be between 18 and 65 years old, live in the community, have had an SCI for 1 or more years [55], use a manual wheelchair as their primary means of mobility, be able to self-propel a manual wheelchair for at least 100 meters; not currently be meeting the physical activity recommendations [62], and be cognitively able to engage in the ALLWheel intervention (Mini-Mental State Exam score ≥25) [63]. Individuals will be excluded if they anticipate a health condition or procedure that contraindicates training, have a degenerative condition that is expected to progress quickly, or are concurrently or planning to take part in another LTPA intervention over the period of the study. Participants will be screened using the Physical Activity Readiness Questionnaire and e-PARmed-X+ [64]. Institutional ethics guidelines will be followed at each of the three sites, and participants will provide informed consent.

##### Procedure

Preferred duration and delivery methods for the ALLWheel intervention will be explored in phase II. However, for the purposes of study planning and budgeting, the intervention length (ie, 6 months) and number of contacts with participants (ie, 14) will be based on the findings of an effective telephone-counseling intervention for improving LTPA for individuals with SCI [19]. Program sessions will be customized to individual LTPA goals, and spouses/partners may be integrated into the ALLWheel program if desired by participants. For the proposed study, a physically active peer coach who has had an SCI for at least 5 years will deliver the ALLWheel intervention. The peer coach will receive comprehensive training through a 2- to 3-day workshop administered by study investigators.

#### Outcome Measures

All assessments will be administered by trained testers at each site who will be trained in a 3-hour workshop facilitated by study investigators (KB, EL).

Descriptive characteristics and sociodemographic information that are known to influence LTPA among individuals with SCI will be collected at baseline (T1) including age, sex, marital status, income, level of SCI, medications, psychological well-being, and social support [9,65-67]. Depression and anxiety will be assessed using the 14-item Hospital Anxiety and Depression Score [68,69], and social support will be assessed using the 6-item Interpersonal Support Evaluation List [70,71].

##### Feasibility Indicators

Feasibility indicators related to process, resources, management, and treatment will be collected throughout study [72]. A description of feasibility indicators, how they will be measured, and the parameters for success are described in Multimedia Appendix 1. Testers at each site will administer all outcome measures at baseline (T1), postintervention (T2), and 3 months postintervention (T3). The selected outcomes are reflective of important theoretical variables known to influence LTPA uptake, adherence, and retention. Additional outcomes may be identified during phases I and II.

##### Actigraphy

The primary outcome, LTPA, will be measured objectively using actigraphy, a noninvasive method of monitoring human activity using a small and lightweight accelerometry-based activity monitor (Actigraph GT3X+, ActiGraph LLC) that can be worn on the body of the wheelchair user and on the wheelchair without impeding movement [73]. The monitor contains an accelerometer that is sensitive to motion in all directions, and data are stored in the monitor as activity counts [74]. Time between sampling units (epochs) will be set at 15 seconds, allowing the greatest sensitivity for low-intensity activity [74]. Concurrent validity and reliability have been established [75,76]. Further validation for the use of actigraphy to distinguish between low and moderate intensities of LTPA among individual manual wheelchair users, including manual wheelchair users with SCI, is available elsewhere [77].

Upon completion of all secondary outcomes (subjective self-reports) at each time point, the tester will provide participants with 2 actigraphs (one will be positioned on the rear wheel of the manual wheelchair in a waterproof enclosure; the other will be worn on the nondominant arm). Participants will be asked to wear the actigraph at all times over a 7-day period except during sleep, bathing, or swimming. Participants will record the time the actigraph was put on and taken off using a log. The tester will obtain the actigraph and log from the participant at the end of the 7-day period. Only data from the days in which the actigraphs are worn for at least 13 hours per day will be included in the analysis [78]. Data will be converted to mean activity counts per hour (ie, bouts per hour).

Secondary outcomes reflect the proposed theoretical impacts of the ALLWheel intervention (ie, the relationship between LTPA behavior) and psychological determinants of behavior change (eg, motivation, autonomy support, and satisfaction of psychological need for LTPA). The secondary outcomes will help to discern a clinically important impact of the ALLWheel intervention.

##### Leisure-Time Physical Activity Questionnaire

Self-reported LTPA behavior will be measured using the 7-day Leisure-Time Physical Activity Questionnaire for adults with SCI [79]. Since actigraphy may not capture the intensity of some activities (eg, weightlifting) and they cannot be worn while swimming, participants will also be asked to recall the frequency (number of bouts) and duration (minutes per bout) of light, moderate, and heavy intensity LTPA over the past 7 days. Acceptable test-retest reliability and construct validity have been documented among adults with SCI [80,81].

##### Treatment Self-Regulation Questionnaire

Motivation to participate in LTPA will be evaluated using the 15-item Treatment Self-Regulation Questionnaire [82], which is designed to measure the degree of autonomous self-regulation to participate in healthy behaviors. Reasons for engaging in or changing health behaviors are scored using a 7-point Likert scale ranging from 1 (not true at all) to 7 (very true). Three subscales assess 6 forms of motivation, including autonomous regulation (identified, integrated, and intrinsic motivations), controlled regulation (external and introjected motivations), and amotivation. The questionnaire has been validated for assessing motivation for engaging in exercise [83]. Since the purpose of this study is to assess participation in physical activity that one engages in during their free time, wording for *exercise* will be changed to LTPA.

##### Leisure-Time Barrier Self-Efficacy Scale

Self-efficacy to overcome salient barriers to LTPA participation (eg, transportation problems, bad weather, pain, fatigue) will be assessed using a 6-item Leisure-Time Barrier Self-Efficacy Scale. The scale has been used in previous research with SCI [84-86] with evidence of high reliability and validity [84] and acceptable internal consistency [81].

##### Psychological Need Satisfaction in Exercise Scale

Satisfaction of the psychological needs for LTPA will be assessed using the Psychological Need Satisfaction in Exercise Scale [87]. Participants are asked to rate 18 items that reflect how a person may feel during physical activity using a 6-point Likert scale. A mean score will be calculated for autonomy, competence, and relatedness.

##### Wheelchair Outcome Measure

The Wheelchair Outcome Measure is a semistructured interview that allows participants to select important wheelchair-oriented participation goals. Participants are asked to identify 2 to 5 goals and evaluate their current satisfaction with participation in each goal (on a scale from 0 to 10). Participation goals are incorporated into the intervention. The instrument demonstrates good reliability and validity in use among individuals with SCI and older adults [88,89].

#### Data Analysis

Analyses will consider study feasibility indicators and primary and secondary outcomes. Means and standard deviations (continuous variables) and frequencies and proportions (categorical variables) will be used to summarize all data. Feasibility outcomes (objective IIIa) will be treated as binary, with *success* indicating the protocol is sufficiently robust to move forward with an RCT with only small or no adaptation required and *revise* indicating a need for changes before proceeding (see Multimedia Appendix 1). Controlling for confounding and within-subject changes from baseline to postintervention and from baseline to follow-up in LTPA behavior will be determined using paired sample *t* tests (or nonparametric equivalent) (objective IIIb). Paired sample *t* tests will be used to evaluate within-subject change scores from baseline to postintervention and from baseline to follow-up for self-reported LTPA, motivation, LTPA barrier self-efficacy, autonomy support, satisfaction of the psychological needs for LTPA, satisfaction with participation in meaningful activities, and controlling for confounding (objective IIIc). Exploratory analyses (objective IIId) will be conducted to investigate the strength and direction of the relationships between sociodemographic and epidemiological factors and primary and secondary outcomes, looking for moderate to strong relationships [90].

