## Discussion

### Principal Findings

The ALLWheel intervention presents an innovative approach to targeting change in LTPA for individuals with SCI. Guided by the tenets of two behavior change theories (ie, self-determination theory and social cognitive theory), conception of ALLWheel will integrate important psychological precursors to LTPA including autonomy, relatedness, competence/self-efficacy, and motivation [29-33]. Furthermore, development of the ALLWheel intervention and study protocol will follow the Medical Research Council framework for developing and evaluating complex interventions [45], which will ensure that ALLWheel is evidence-based. Development of the ALLWheel program will also involve knowledge users (eg, individuals with SCI, community organizations, clinicians) throughout all aspects of development, evaluation, and implementation, ensuring an integrated approach to knowledge translation. Finally, a feasibility evaluation will allow for refinement of the intervention and iterations of the protocol to maximize its impact.

Although the LTPA needs of individuals with SCI are not fully understood, there is reason to believe that including peers in intervention delivery may have benefits [39]. Furthermore, a program delivered using a smartphone has the potential to overcome many existing barriers to LTPA for individuals with SCI and allows for integration of an important face-to-face component (ie, through video-conferencing). The application of digital peer training (ie, digital person-to-person training facilitated by a peer using smartphone technology [91]) could maintain the benefits of telephone-delivered interventions (eg, increased geographic reach [19-21]), incorporate human support (ie, an important predictor of effect and adherence of behavior change interventions [91]), ensure individually tailored programs, and facilitate the implementation of important psychological factors [31-33]. Evaluating outcomes of autonomy, motivation, and self-efficacy will allow for exploration of theorized relationship between psychological factors and LTPA, which will provide crucial information for refinement of the intervention before conducting a larger RCT.

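### Objective IIId is framed as mediation and moderation, but its stated analysis addresses neither, and picking out the larger associations is unreliable with 12 people in one group

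*Protocol article*

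**What the plan says.** Objective IIId in the Protocol article is to "explore potential mediating and moderating relationships between LTPA and sociodemographic factors, epidemiological variables, and all secondary outcomes". Under Phase III, Data Analysis, the sentence labelled with this objective says that the exploratory analyses will "investigate the strength and direction of the relationships between sociodemographic and epidemiological factors and primary and secondary outcomes, looking for moderate to strong relationships". No numerical cut-off is given, only a literature reference. Neither a mediation model nor an interaction term is mentioned.

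The Phase III Design section states: "A three-site, pre-post feasibility study will be done". No comparison group is described. Participant Recruitment states: "A convenience sample of 12 community-dwelling individuals living with SCI will be recruited", and supports that number with a rule of thumb that "10 to 15 participants may be adequate to detect feasibility in a pilot study".

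Principal Findings, in the Discussion, says that measuring autonomy, motivation and self-efficacy will allow the theorised link between psychological factors and LTPA to be explored, "which will provide crucial information for refinement of the intervention before conducting a larger RCT".

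**The concern.** There are two separate problems.

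The first is a mismatch between objective and analysis. Mediation concerns an indirect path: the intervention changes a psychological factor, which in turn changes LTPA. Moderation concerns an effect that differs by level of a third variable. The strength and direction of an association between a background factor and an outcome is neither. The relation that the behaviour-change theory needs, psychological change against LTPA change, is not clearly among the pairs that the analysis sentence lists.

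The second is the selection rule. Looking for associations above a certain size, in a sample where chance alone often produces that size, picks out sampling noise along with any real signal. A report that shows only the larger values would give readers no means of telling the two apart. Ideas carried into the design of the RCT could then rest on associations that would not recur.

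**Working it through.** **Objective against analysis**

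| | Objective IIId | Data Analysis sentence for IIId |
|---|---|---|
| Question | Mediation and moderation | Strength and direction of relationships |
| Variables set against LTPA | Sociodemographic factors, epidemiological variables, all secondary outcomes | Sociodemographic and epidemiological factors |
| Psychological outcomes | Related to LTPA | Listed, with LTPA, among the outcomes that the factors are related to |
| Selection | None | By size, no cut-off printed |

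Both sentences are in the article, and the second carries the objective's label. The mismatch is therefore something the article states, not a detail left to a fuller document.

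**Inputs for the size filter**

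- n = 12, from Participant Recruitment. This figure rests on a feasibility rule of thumb, with no power calculation to reproduce.
- Measure of strength: Pearson correlation r. This is an assumption, because the text does not name the measure.
- Cut-off: not printed, so a range of 0.3 to 0.7 is assumed.
- Number of pairs: assumed. Outcome Measures names 8 baseline factors (age, sex, marital status, income, level of injury, medications, psychological well-being, social support). Actigraphy plus five instruments makes 6 outcomes, so 8 × 6 = 48. A wider screen of 9 × 9 = 81 is taken as the upper figure. Counting the three motivation subscales and the three need-satisfaction scores separately gives 10 outcomes and 8 × 10 = 80, which is close to it.

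**Chance of reaching each cut-off when the true correlation is zero**

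t = r × √((n − 2)/(1 − r²)) with n − 2 = 10 degrees of freedom, two-sided. For r = 0.5, t = 0.5 × √(10/0.75) = 1.83, giving P = 0.098.

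| Absolute r at least | t | Null probability | Expected among 48 null pairs | Expected among 81 null pairs |
|---|---|---|---|---|
| 0.3 | 0.99 | 0.343 | 16.5 | 27.8 |
| 0.5 | 1.83 | 0.098 | 4.7 | 7.9 |
| 0.6 | 2.37 | 0.039 | 1.9 | 3.2 |
| 0.7 | 3.10 | 0.011 | 0.5 | 0.9 |

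If the 48 pairs were independent, the chance of at least one reaching 0.5 would be 1 − (1 − 0.098)^48, about 99%. The expected counts do not need independence. With only 10 people analysed, the per-pair chances rise to 40% at 0.3 and 14% at 0.5.

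**Precision of one estimate**

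Fisher z for r = 0.5: atanh(0.5) = 0.549, with standard error 1/√(12 − 3) = 0.333. The limits are 0.549 ± 1.96 × 0.333, or -0.104 to 1.203, which transform back to -0.10 and 0.83. For r = 0.3 the interval is -0.33 to 0.75. The two-sided 5% critical value at n = 12 is 0.576.

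**What 12 people could detect**

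Simulated power for one true correlation, two-sided 5%, is about 16% at 0.3 and 40% at 0.5. A joint-significance mediation test with assumed path coefficients of 0.39 or 0.59 has about 4% or 14%. Naming a mediation model would therefore not by itself rescue the objective in this sample.

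**The case against.** The objective is worded as exploring potential relationships, it is the fourth of four exploratory objectives, and 12 participants are justified for feasibility alone. The binary classification that decides whether to move to an RCT is tied to objective IIIa, and no printed rule uses IIId. All of this stands and limits the consequence. It does not make the stated analysis an answer to the stated objective.

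The analysis sentence might be read as covering relations among all the listed sets, including psychological outcomes with LTPA. That reading would agree with the objective and the Discussion. It is possible, so the fair statement is that the pair is not clearly included. It would also enlarge the screen.

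A pre-post study has a within-person time contrast, and baseline factors can be set against change. That is so, but without a comparator such associations cannot be attributed to the intervention, and the analysis sentence does not mention change scores.

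The cut-off could be strict: at 0.7 chance produces only 1% of pairs. The filter as worded, however, begins at moderate values, where the chance rate is likely to be higher.

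Two stronger readings are tempting. A reader might infer that most of the flagged relations would be false. The documents do not support this: the counts above assume that every pair is null, whereas Outcome Measures says the baseline characteristics were chosen because they are known to influence LTPA. The false share depends on how many relations are real, which is not given. A reader might also infer that the plan calls the flagged mediators and moderators crucial. It does not: that remark in Principal Findings concerns the exploration of psychological factors and LTPA, not the screen of sociodemographic factors.

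**Conclusion.** The point holds in a limited form. The analysis stated for objective IIId cannot show mediation or moderation of an intervention effect in one group of 12 people. It does not clearly include the psychological-outcome against LTPA relation that the article wants to use for refinement. Filtering by size is unreliable at this sample size: per null pair, chance reaches 0.3 in 34%, 0.5 in 10%, 0.6 in 4% and 0.7 in 1%. Over 48 to 81 null pairs, that is about 16 to 28 at 0.3 and about 5 to 8 at 0.5.

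These figures assume Pearson correlations, cut-offs that the article does not print, and a pair count built from its lists of factors and outcomes. They are not an estimate of how many flagged relations would be false. They are also no criticism of 12 participants as a feasibility sample, and the decision to proceed to an RCT does not depend on IIId. The matter is worth correcting because the wording invites a reader to treat size-selected associations as evidence on mechanism.

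**What to change.** 1. Restate objective IIId as descriptive and hypothesis-generating, and leave mediation and moderation to the RCT, where there is a randomised contrast.
2. Name a few pairs in advance: change from T1 to T2 in autonomous motivation, in barrier self-efficacy and in need satisfaction, each against change from T1 to T2 in LTPA.
3. Report every estimate examined, with its 95% CI.
4. Delete the clause that looks for relationships above a certain size.

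The cost is the wording of one objective and one analysis sentence. All outcome measures are already scheduled at T1 and T2, so no visit or measurement is added and the feasibility objective is untouched. The drawbacks are a less ambitious objective and intervals that stay as wide as those shown above. Naming the pairs limits the number of chance findings but does not sharpen any single estimate.

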## Results

This project is funded by the Craig H Neilsen Foundation, the Fonds de Recherche du Québec–Santé, and the Canadian Disability Participation Project. Approval has been obtained from the university research ethics boards at all sites for all phases of the study. Phase I scoping and systematic reviews have been completed, and manuscript preparation is underway. Phase II focus groups and Delphi surveys are near completion, and manuscript preparation is underway. Phase III pilot and feasibility evaluation is currently underway. All study staff have been hired and trained at all sites, and recruitment and data collection are ongoing. Four peer trainers have been recruited and trained, and recruitment for phase III was completed in September 2018.

## Discussion

### Principal Findings

The ALLWheel intervention presents an innovative approach to targeting change in LTPA for individuals with SCI. Guided by the tenets of two behavior change theories (ie, self-determination theory and social cognitive theory), conception of ALLWheel will integrate important psychological precursors to LTPA including autonomy, relatedness, competence/self-efficacy, and motivation [29-33]. Furthermore, development of the ALLWheel intervention and study protocol will follow the Medical Research Council framework for developing and evaluating complex interventions [45], which will ensure that ALLWheel is evidence-based. Development of the ALLWheel program will also involve knowledge users (eg, individuals with SCI, community organizations, clinicians) throughout all aspects of development, evaluation, and implementation, ensuring an integrated approach to knowledge translation. Finally, a feasibility evaluation will allow for refinement of the intervention and iterations of the protocol to maximize its impact.

Although the LTPA needs of individuals with SCI are not fully understood, there is reason to believe that including peers in intervention delivery may have benefits [39]. Furthermore, a program delivered using a smartphone has the potential to overcome many existing barriers to LTPA for individuals with SCI and allows for integration of an important face-to-face component (ie, through video-conferencing). The application of digital peer training (ie, digital person-to-person training facilitated by a peer using smartphone technology [91]) could maintain the benefits of telephone-delivered interventions (eg, increased geographic reach [19-21]), incorporate human support (ie, an important predictor of effect and adherence of behavior change interventions [91]), ensure individually tailored programs, and facilitate the implementation of important psychological factors [31-33]. Evaluating outcomes of autonomy, motivation, and self-efficacy will allow for exploration of theorized relationship between psychological factors and LTPA, which will provide crucial information for refinement of the intervention before conducting a larger RCT.

Including expert stakeholders (ie, individuals with SCI, clinicians, and community partners) in the development of a theory-based ALLWheel intervention is an integral component of this research program [54]. Obtaining consensus from our stakeholders and knowledge users will ensure that we develop a comprehensive LTPA intervention that is desirable to the people for whom it is intended. Evaluating the feasibility of the intervention in pre-post study design will allow for feedback from the stakeholders and modifications before implementing a larger more expensive effectiveness trial.

ALLWheel has potential for large geographic reach to individuals of various ages, and determining the feasibility of administering the program in English and French may lead to translation in other commonly used languages in Canada. Future studies can estimate cost effectiveness, measure long-term retention, and assess impact on the known health benefits.

